### Plans to promote participant retention and complete follow-up {18b}

Patients will be sent an appointment for clinical follow-up by mail. Administration of patient follow-up will be conducted by a research nurse with overview of the entire study population (checklists). All data that has been collected up to the point of discontinuation will be considered consensual and used in the analyses. After discontinuation no further data will be collected from the study participant which will be considered “lost to follow-up”.

### Data management {19}

Data will be collected on case report forms (CRF) for each step of the study (inclusion, intervention, postoperative care, and each follow-up separately). The forms will be coded with the individual randomisation number and stored in locked cabinets with logged access only available to the researchers and administrators responsible for the trial. When data collection is complete, the CRF will be transferred to an Access® (Microsoft®, Redmond, WA, USA) database, stored in encrypted form on the intranet of Region Västerbotten, with the password only available to the responsible researchers and administrators. Microsoft Access® is specially designed for databases and includes rules and limitations for data input and analyzation, which prevents duplicates and significantly decreases the risk for data corruption. CRFs are checked by an experienced research administrator before entering data to the database. The Access® database is designed so that all parameters included are limited to realistic values to promote data quality.

### Confidentiality {27}

Patients that are potential candidates for inclusion are cared for under the national healthcare system for their stoma. As soon as a patient, stoma nurse, or any other healthcare provider notices a stoma problem that could be a parastomal hernia, that patient will be referred to one of the surgeons responsible for handling of patients in the study. This procedure is the same as for patients not taking part in the study, and all information on the management of potential study candidates is stored in the medical records as is normal clinical practice. For more information on how confidentiality is assured, please see the “Data management {19}”.

### Plans for collection, laboratory evaluation and storage of biological specimens for genetic or molecular analyses for this trial/future use {33}

Patients who participate in the ancillary study investigating tissue biology in parastomal hernia repair undergo biopsy of the abdominal wall fascia during the primary intervention. This biopsy is analysed for collagen structure and metabolism, tissue composition and protein expression. Postoperatively and during the clinical follow-up, blood samples are taken to analyse markers monitoring connective tissue turnover and tissue remodelling processes.

A subgroup of patients will also be offered postoperative biopsy of the implanted reinforcement material via a transcutaneous ultrasound-guided needle biopsy adjacent to the stoma.

All tissue samples will be stored fresh-frozen in ultra-low temperature freezers (at Biobanken Norr) until analysis.

## Statistical methods

### Statistical methods for primary and secondary outcomes {20a}

Generally, statistical methods used in the study are aimed to describe and compare the outcomes between the study groups. Based on the characteristics of each outcome, chi-squared test, Mann-Whitney *U* test and Student’s *t* test are used to evaluate the statistical significance of the different outcomes.

#### Rate of complications and recurrences

Data are presented descriptively and the results from each study group are compared with chi-squared test.

#### Pain and quality of life

Evaluated with VHPQ and EORTC CR29 and CR30 respectively and answers are reported and scored according to their specific scoring manuals. Comparisons between the study groups are done with Mann-Whitney *U* test or Student’s *t* test by convention.

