#### Secondary outcomes:

Recurrence. Parastomal hernia recurrence will be assessed clinically, with stomal ultrasound and/or CT-scan.Pain. All subjects will complete the Ventral Hernia Pain Questionnaire (VHPQ) to assess and compare preoperative pain ratings related to daily activities with ratings at all clinical follow-ups [18].Quality of life. All subjects will complete the European Organisation for Research and Treatment of Cancer questionnaire module for colorectal cancer (EORTC CR29) as well as the European Organisation for Research and Treatment of Cancer core quality of life questionnaire (EORTC QLQ-C30) to assess and compare different aspects of quality of life pre- and postoperatively at all clinical follow-ups [19–21].Health economics. Cost-effectiveness for each treatment arm. The total cost of each method will be calculated from the hospital healthcare costs system based on duration of surgery, cost of operating time and equipment, duration and cost of anaesthesia and cost of complications including infection, bleeding, seroma and fistula formation.

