### Sample size {14}

The power calculation is based on the primary outcome with an estimated short-term complication rate of 15% in the FTSG-group and in 40% in the synthetic mesh group. To achieve 80% power and 95% significance level, 39 patients are required in each arm. To compensate for loss to follow-up over the relatively long follow-up time, we plan for 90 patients (45 in each arm) to be included in the trial.

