#### Health economics

Data are presented descriptively and the results from each study group are analysed with Mann-Whitney *U* test or Student’s *t* test depending on the distribution of the specific variable.

The study assumes a significance level of 0.05.

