### Methods for additional analyses (e.g. subgroup analyses) {20b}

Regression analysis is used to explore any relationships between patient characteristics and outcome. Depending on the characteristics of the outcome, different concepts for regression analyses are used. Linear regression is used for continuous variables, logistic regression for dichotomous variables and ordinal regression for ordinal outcome variables.

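### Pain and quality of life are compared by unadjusted two-sample tests although the preoperative scores are collected, which gives up precision at no saving

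*Protocol article*

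**What the plan says.** Under Pain and quality of life: "Comparisons between the study groups are done with Mann-Whitney" U test or Student's t test, with convention given as the only basis for choosing between them. Section {20a} lists chi-squared, Mann-Whitney and t tests, which "are used to evaluate the statistical significance of the different outcomes". Neither place names a baseline covariate.

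The baseline exists. Table 1 under Participant timeline {13} schedules both questionnaires at enrolment and at 3, 12 and 36 months, and section {18a} confirms preoperative collection. (The label CR30 in the table and the analysis section is read here as QLQ-C30.) Secondary outcomes describes VHPQ as used "to assess and compare preoperative pain ratings related to daily activities with ratings at all clinical follow-ups", and the EORTC questionnaires as used "to assess and compare different aspects of quality of life pre- and postoperatively at all clinical follow-ups".

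Regression appears only in section {20b}: "Regression analysis is used to explore any relationships between patient characteristics and outcome". That is exploration of prognostic factors, not a baseline-adjusted treatment comparison.

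**The concern.** The outcomes are framed around the preoperative rating, but the named analysis has no stated place for it. The text does not say whether the tested variable is the follow-up score or the change from baseline.

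This matters because the hypothesis under Objectives {7} claims greater comfort as well as greater safety, and pain and quality of life are the natural measures of comfort. The trial is sized on complications alone. With 78 to 90 patients these comparisons have little power to spare, and a chance difference between arms before surgery could colour the result.

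**Working it through.** **Inputs from the protocol article.** 39 evaluable patients per arm and 45 per arm planned (Sample size {14}); significance level 0.05 (end of Health economics), taken as two-sided here because the sidedness is not stated; power 80%.

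**Assumptions.** The correlation r between preoperative and follow-up score is not in the document, so it is shown at 0.3, 0.5 and 0.7. The SD is taken as equal before and after surgery, and the relation as linear.

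**The plan's own figure.** No SD, effect size or power is given for pain or quality of life. The only stated size is for complications, 15% against 40%: "To achieve 80% power and 95% significance level, 39 patients are required in each arm". With mean proportion 0.275, n = [z_α√(2 × 0.275 × 0.725) + 0.8416√(0.15 × 0.85 + 0.40 × 0.60)]² / 0.25².
- One-sided, z_α = 1.645: (1.039 + 0.510)² / 0.0625 = 38.4, so 39, which matches.
- Two-sided, z_α = 1.960: (1.238 + 0.510)² / 0.0625 = 48.9, so 49.

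The one-sided basis is a separate matter. Here 39 serves only as the number per arm.

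**Step 1, precision.** Take the variance of the arm difference in follow-up scores as 1. For change scores it is 2(1 − r); for ANCOVA it is 1 − r². The ratio of ANCOVA to change scores is (1 + r)/2. The difference detectable on follow-up scores is (1.960 + 0.8416) × √(2/39) = 0.634 SD. For the other two analyses, multiply by the square root of the variance.

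| r | Variance: follow-up / change / ANCOVA | Detectable difference, SD: follow-up / change / ANCOVA | ANCOVA cut vs follow-up | ANCOVA cut vs change |
|---|---|---|---|---|
| 0.3 | 1 / 1.40 / 0.91 | 0.63 / 0.75 / 0.61 | 9% | 35% |
| 0.5 | 1 / 1.00 / 0.75 | 0.63 / 0.63 / 0.55 | 25% | 25% |
| 0.7 | 1 / 0.60 / 0.51 | 0.63 / 0.49 / 0.45 | 49% | 15% |

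Against follow-up scores, ANCOVA on 78 patients is worth 78/(1 − r²) = 86, 104 or 153 patients.

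**Step 2, power for an assumed 0.5 SD difference.** Power is Φ(0.5/√(2f/n) − 1.960), with f the variance factor above.
- 39 per arm: follow-up scores 60%; change scores 46%, 60%, 81%; ANCOVA 64%, 72%, 87%.
- 45 per arm: follow-up scores 66%; change scores 52%, 66%, 87%; ANCOVA 70%, 78%, 91%.

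**Step 3, chance imbalance.** The standard error of a baseline difference is √(2/39) = 0.23 SD, or √(2/45) = 0.21 SD, so an imbalance of 0.2 SD would be unremarkable. On follow-up scores it carries 0.2r = 0.06, 0.10 or 0.14 SD into the comparison. On change scores it is over-corrected by 0.2(1 − r) = 0.14, 0.10 or 0.06 SD. ANCOVA removes it using the estimated slope.

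**Limits.** The formulas concern mean differences of roughly continuous scores and ignore the small cost of estimating the slope. They put no figure on Mann-Whitney comparisons or ordinal items.

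**The case against.** The strongest reply is that this is a matter of efficiency, not an error. In a randomised trial both tests hold their type I error over repeated randomisation, the outcomes are secondary, and covariates are commonly left to an analysis plan that is not shown. The first two points stand. The third does not answer the concern: the article does not leave the method open but names unadjusted tests, so an analysis plan using ANCOVA would depart from it.

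The size of the loss is also uncertain. Patients enter because of symptoms that the operation is meant to relieve, so r may be low. At 0.3 the gain over follow-up scores is small. That stands.

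Three stronger readings are tempting and not supported:
- A reader might infer that baseline imbalance is certainly left uncorrected. The wording under Secondary outcomes also allows a test of changes, in which case baseline is used, but over-corrected.
- A reader might infer a separate test at each visit. The article names no repeated-measures model, but it does not state this either.
- A reader might infer that the unblinded analysts may choose freely between the two tests. Section {20a} ties the test to the characteristics of each outcome, and Health economics ties the same pair to the distribution. The reference to convention is loose wording, and the rule should be stated, but it is not an open licence.

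**Conclusion.** The concern holds as a loss of precision together with an unstated choice of tested variable, not as an invalid analysis. Whichever variable is meant, ANCOVA on the preoperative score has the smaller variance: by 9% to 49% against follow-up scores and by 35% to 15% against change scores as r runs from 0.3 to 0.7. The two trends run in opposite directions, so no single figure can be quoted until the tested variable is stated. All figures rest on the assumed r, equal SDs and roughly continuous scores. The primary comparison of complications is unaffected. The change is worth making, but the trial does not stand or fall by it.

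**What to change.** Make the main between-arm analysis of each EORTC scale at 3, 12 and 36 months an ANCOVA with arm and the preoperative score as terms, and report the adjusted mean difference with its 95% confidence interval. For ordinal or skewed VHPQ items, use ordinal regression, already named in section {20b}, or a rank-based analogue, with the baseline rating as covariate. Keep Mann-Whitney as a sensitivity analysis and state which variable it tests.

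A mixed model for repeated measures is optional. Because it draws on patients with incomplete follow-up under a missing-at-random assumption, it would have to be reconciled with the statement in section {20c} that no statistical methods compensate for missing data. ANCOVA at each visit on observed scores avoids that conflict.

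The cost is revised analysis wording, slightly more analysis work and some model assumptions to check. The ordinal models need a feasibility check at this sample size, and patients without a preoperative questionnaire drop out of the adjusted analysis. No extra patients, visits or data are needed.

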#### Health economics

Data are presented descriptively and the results from each study group are analysed with Mann-Whitney *U* test or Student’s *t* test depending on the distribution of the specific variable.

The study assumes a significance level of 0.05.

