### Objectives {7}

The objective of the trial is to compare a novel method of repair for parastomal hernia to one of the best available conventional methods in terms of surgical complications, recurrence, QoL and health economics.

Our hypothesis is that autologous FTSG as reinforcement material in parastomal hernia (PH) repair offers a safer and more comfortable alternative to conventional synthetic mesh material.

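### The distribution-dependent test rule would probably send total cost to Mann-Whitney, which does not compare the mean cost that determines total cost (minor)

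*Protocol article*

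**What the plan says.** Health economics is part of the trial objective: the two repairs are to be compared "in terms of surgical complications, recurrence, QoL and health economics" (Objectives). The list of secondary outcomes promises "Cost-effectiveness for each treatment arm" and defines the cost side: "The total cost of each method will be calculated from the hospital healthcare costs system". The components are duration of surgery, operating time and equipment, anaesthesia, and "cost of complications including infection, bleeding, seroma and fistula formation".

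The analysis text is the short Health economics paragraph under Statistical methods. Data are presented descriptively, and then "the results from each study group are analysed with Mann-Whitney" or Student's t, the "test depending on the distribution of the specific variable". Skewness is not mentioned, but a rule of this form is normally read as t for roughly normal variables and Mann-Whitney otherwise.

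**The concern.** The quantity of interest is the total cost of each method. That equals the number of patients times the arithmetic mean cost, so a comparison of total cost is a comparison of means. Mann-Whitney instead addresses whether a patient in one arm tends to cost more than a patient in the other. It registers a small difference that nearly every patient carries, and gives little weight to how large a rare, expensive event is.

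Cost in this trial has both parts. Every patient has theatre and anaesthesia costs, and a minority has complication costs. If the graft operation costs somewhat more for everyone while complications are fewer, the two parts pull in opposite directions, and the rank test and the mean difference can then disagree. At stake is whether the cost result says which method is cheaper.

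**Working it through.** **Inputs from the protocol.** Sample size gives an "estimated short-term complication rate of 15% in the FTSG-group and in 40% in the synthetic mesh group" and 45 patients per arm. The significance level is 0.05. The document states no cost figure, so there is no plan figure to reproduce.

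**Assumed inputs.** These are illustrations and do not come from the protocol.
- Index cost is lognormal with log-SD 0.2. The median is 100 with mesh and 100 × (1 + premium) with the graft.
- Complication cost is lognormal with median 200 and log-SD 0.6, added only in patients with a complication.

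**Mean costs.** The mean of a lognormal is median × exp(log-SD²/2).
- Mean index cost, mesh: 100 × exp(0.02) = 102.0.
- Mean complication cost: 200 × exp(0.18) = 239.4.
- Mesh arm: 102.0 + 0.40 × 239.4 = 197.8.
- Graft arm: 102.0 × (1 + premium) + 0.15 × 239.4 = 102.0 × (1 + premium) + 35.9.

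**Simulated trials.** 45 per arm, two-sided 0.05, Mann-Whitney against Welch's t. With equal arm sizes Welch and Student have the same t statistic and differ only in degrees of freedom. Percentages carry simulation error of about one or two points.

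| Graft index premium | Mean cost, graft vs mesh | Graft cheaper by | Mann-Whitney: mesh dearer | Welch: mesh dearer |
|---|---|---|---|---|
| 0% | 137.9 vs 197.8 | 60 | 53% | 59% |
| 10% | 148.1 vs 197.8 | 50 | 14% | 44% |
| 20% | 158.3 vs 197.8 | 40 | 3% | 28% |
| 30% | 168.5 vs 197.8 | 29 | 0.5% | 17% |

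At a 20% premium the probability that a graft patient costs more than a mesh patient is 0.50, so the ranks see no difference while the means differ by 40. At 30% Mann-Whitney is significant in the wrong direction (graft dearer) in about 13% of trials. On means, the graft stays cheaper until 102.0 × premium = 0.25 × 239.4, a premium of about 59%. Under these assumptions, then, ranks and means point in opposite directions for premiums between roughly 20% and 59%.

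**Second check, with mean costs set equal.** Take the mean index cost of a mesh operation as 1 (CV 15%), with complication cost lognormal with CV 1. Means are equal when premium = (0.40 − 0.15) × mean complication cost. For example, 1 + 0.10 + 0.15 × 0.4 = 1.16 and 1 + 0.40 × 0.4 = 1.16. For premiums of 10%, 15%, 20% and 25% (mean complication cost 0.4, 0.6, 0.8 and 1.0), Mann-Whitney is significant in about 10%, 20%, 33% and 46% of trials, nearly always as graft dearer. Welch stays at about 5% to 6%.

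**The case against.** The rule is conditional. Student's t is the other branch and does compare means, the word skewed does not appear, and the descriptive presentation can show mean and total cost whichever test follows. The rule also covers several variables, and for durations such as operating time a distribution-dependent choice is unremarkable. All of this stands. It limits the point to total cost under skew, which complications in a minority of patients make very likely.

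The premium is also an assumption. The Background suggests that the graft could be the less expensive material, and equipment cost includes a purchased mesh in one arm only. With no premium the two tests nearly agree. This stands too, so no single row of the table should be read as a forecast.

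Two stronger readings are tempting and not supported:
- A reader might infer that the plan cannot deliver cost-effectiveness because no effect is paired with cost. A test on cost alone indeed does not give it, but the effect measure and incremental analysis are details that a condensed article may leave to a fuller plan, and nothing here rules them out.
- A reader might infer that readmissions and reoperations, which are recorded at follow-up, are left out of the costs. The complication list is introduced as inclusive and is not exhaustive, so nothing excludes them.

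**Conclusion.** The point holds in limited form. The article fixes a rule whose natural reading sends total cost to a rank test, while the stated quantity depends on arithmetic means. That mismatch does not depend on any cost assumption, but its practical size does. Under the main illustration, the chance of finding mesh dearer is 53% versus 59% (Mann-Whitney versus Welch) with no premium and 3% versus 28% at a 20% premium. A wrong-direction result appears in about 13% of trials at 30%. It would go too far to conclude that the trial will name the wrong arm as cheaper: that needs a sizeable graft premium, and the protocol states none. Severity is minor, because this is a secondary outcome and the primary comparison is untouched.

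**What to change.** For total cost, whatever its distribution, report the difference in arithmetic mean cost per patient with a non-parametric bootstrap (or Welch) 95% confidence interval, and remove the Mann-Whitney option for cost. If the outcome is to keep the name cost-effectiveness, relate the cost difference to a named effect already collected, with cost and effect bootstrapped jointly. Otherwise call it a cost comparison.

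This changes a few lines of analysis text and needs no new data or patients. The downside is that the interval may be wide at this sample size. In the table, even the test of means detects the difference in only 17% to 59% of trials, and an honest interval would show that uncertainty.

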### Interim analyses {21b}

After 30 operations have been performed, a safety analysis is performed. It is conducted by a scientifically experienced researcher (at least assistant professor) with long clinical experience of abdominal wall surgery but has no connection with the study. The safety analysis is based on CRF data and complications graded Clavien-Dindo 3b or worse based on information from copies of the medical records from postoperative care on the ward and clinical follow-ups. Should serious or unexpected complications associated with study allocation arise, the study will be interrupted by the surgeon performing the safety analysis. Safety analysis data will otherwise not be available to the responsible researchers or surgeons participating in the study.

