The study intervention was developed with the aid of 3D-models reconstructed from computerised tomography (CT) scans of patients suffering from parastomal hernia. Four pilot patients have then been operated on in a feasibility study which showed no procedure-related complications [15].

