### Composition of the data monitoring committee, its role and reporting structure {21a}

A safety analysis will be performed by an independent senior surgeon after 30 operations (more details under item 21b). This person will be certified to terminate inclusion in the study if undefendable differences between the treatment arms are found or if repeated method related severe adverse events are found in any of the study arms. If no such signs are found, results from the safety analysis will not be propagated to the steering board or participating centres. No other progressive data monitoring will be performed in this trial.

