### Frequency and plans for auditing trial conduct {23}

Other than the safety analysis, no other auditing is planned.

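### The only independent safety review comes after 30 operations and further monitoring is ruled out, so no planned review by arm covers the other 60 patients or later events in the first 30

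*Protocol article*

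**What the plan says.** Interim analyses {21b} sets the trigger: "After 30 operations have been performed, a safety analysis is performed". An experienced researcher unconnected with the study carries it out. It uses case report form data and complications of Clavien-Dindo grade 3b or worse, "based on information from copies of the medical records from postoperative care on the ward and clinical follow-ups". No minimum follow-up is attached to the 30 patients.

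The power to act is described in two places and worded differently:

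- {21b}: "Should serious or unexpected complications associated with study allocation arise, the study will be interrupted by the surgeon performing the safety analysis".
- Composition of the data monitoring committee {21a}: "This person will be certified to terminate inclusion in the study". The grounds are an indefensible difference between the arms, or "if repeated method related severe adverse events are found in any of the study arms".

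Two sentences close off anything further. {21a} ends with "No other progressive data monitoring will be performed in this trial". Frequency and plans for auditing trial conduct {23} says "Other than the safety analysis, no other auditing is planned".

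On prior experience, Background and rationale {6a} says of the graft technique: "Four pilot patients have then been operated on in a feasibility study which showed no procedure-related complications".

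**The concern.** The independent surgeon is the only person outside the trial team who is given authority to end inclusion, and uses it once, one third of the way through the planned operations. One of the grounds in {21a} is repetition of severe events, which takes patients and time to show itself. After the look, events go into the medical records and case report forms (Reporting adverse events and harm {22}), but no planned independent comparison by arm follows.

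The setting makes this matter. The trial compares a new use of skin grafting with a synthetic mesh for which the background names serious complications. The Discussion gives patient safety as the primary goal, and Recruitment {15} expects further centres to be invited, so new teams may start after the only look. At stake is whether an imbalance in severe harm that builds up over operations 31 to 90 would be put before someone independent who is entitled to act on it.

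**Working it through.** **Inputs from the protocol article.** Total 90, 45 per arm (Sample size {14}). Allocation 1:1 (Trial design {8}). One look after 30 operations ({21b}). Follow-up at 3, 12 and 36 months (Outcomes {12}). Recruitment from December 2019, aiming to finish on 31 December 2025, about 72 months (Trial status).

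**Coverage.** 90 − 30 = 60 patients are operated on after the look; 60/90 = 67%.

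**Follow-up available at the look.** Assume uniform accrual. 90 patients in 72 months is one per 0.8 months, so the 30th operation falls at 24 months. Patient i has then been followed for 24 − 0.8i months.

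- At least 3 months: i ≤ 26.25, so 26 of 30.
- At least 12 months: i ≤ 15, so 15 of 30.
- At least 36 months: none.

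These counts depend on accrual, which Trial status says was disrupted:

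| Months to reach 30 operations | Reached 3 months | Reached 12 months | Reached 36 months |
|---|---|---|---|
| 12 | 22 | 0 | 0 |
| 24 | 26 | 15 | 0 |
| 36 | 27 | 20 | 0 |
| 48 | 28 | 22 | 7 |

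**Chance of seeing repeated events in one arm.** The protocol gives no severe-event rate and no number for repetition. I assume a probability p of 5% or 10% that a patient has had such an event by the time of the look, and read repetition as at least 2 events in the arm. Then

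P(X ≥ 2) = 1 − (1 − p)^n − n·p·(1 − p)^(n−1).

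- n = 15, p = 0.05: 1 − 0.463 − 0.366 = 0.171.
- n = 15, p = 0.10: 1 − 0.206 − 0.343 = 0.451.

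Events accumulate, so with a second look at 60 operations the criterion is met at one look or the other exactly when it is met on the combined 30 per arm:

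| Assumed rate | One look, 15 per arm | Second look, 30 per arm | All 45 per arm |
|---|---|---|---|
| 5% | 17% | 45% | 67% |
| 10% | 45% | 82% | 95% |

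**What a clean first look would mean.** With 0 events in 15, the one-sided 95% upper limit is 1 − 0.05^(1/15) = 18%. With 0 in 45 it is 1 − 0.05^(1/45) = 6.4%.

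**Follow-up at a second look.** On the same accrual assumption, the 60th operation falls at 48 months and patient i has 48 − 0.8i months. All of the first 30 would have at least 24 months and 15 of them at least 36. Of all 60, 56 would have reached 3 months and 45 would have reached 12.

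**The case against.** Several stronger readings are tempting, and the documents do not support them.

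- A reader might infer that the stopping criterion cannot operate, or is unlikely to be met. The first look does include clinical follow-up, and at the planned average pace most of the 30 would have had the 3-month visit. The percentages also model only one ground. {21a} allows a stop for a difference between arms, and {21b} sets no number of events. If one event sufficed, the chance of seeing at least one in 15 patients is 1 − 0.95^15 = 54% at a 5% rate and 1 − 0.90^15 = 79% at 10%.
- A reader might infer that the harms named in the background (mesh infection, fistula, bowel erosion) come late and would be mostly unseen at the look. The protocol gives no timing for any of them.
- A reader might infer that nobody sees events after operation 30. Operating surgeons and data analysts are not blinded, the surgeon on call can be unblinded before a reoperation, and a steering committee of clinically active researchers governs the trial while the central office follows its progress. None of this is a planned independent comparison by arm, but it is not nothing.
- The lack of a follow-up window is a lesser matter. About 4 of the 30 would lack a 3-month visit at the planned average pace, and an article may leave a data cut-off to the full protocol.
- The Discussion also cites experience with skin grafts in giant incisional hernia, so the four pilot patients are not the whole background. They are the experience it reports with this technique in parastomal hernia.

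These points narrow the concern without removing it. A single look with further monitoring excluded is stated outright. It is not a detail that the article has merely left out.

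**Conclusion.** The concern holds as a limit on coverage. As written, no planned independent review by arm applies to 60 of the 90 patients, or to events in the first 30 that arise after the look. That part rests on the text alone.

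The 17% and 45%, rising to 45% and 82% with a second look, illustrate scale only. They rest on assumed rates, about 15 and 30 patients per arm, and the reading of repetition as at least 2 events in one arm. The follow-up counts rest on uniform accrual. Neither shows that the first look is worthless or that later events would go unnoticed by the trial team. The weakness should be corrected because the gain is in patient safety and the correction is cheap. It does not bear on the validity of the primary comparison.

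**What to change.** Keep the first review after 30 operations. In {21b} and {21a}, add a repeat of the same confidential, harm-only review by the same independent surgeon after about 60 operations. It should use all ward and follow-up data accrued by then on every operated patient, including updated follow-up of the first 30. Amend the sentence in {21a} that excludes further data monitoring, and bring {23} into line. Because {21a} and {21b} describe the grounds for stopping differently, they should be reconciled in the same amendment.

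I would not postpone the first look until the 30th patient's 3-month visit. At the planned average pace (90/72 = 1.25 operations per month) that would put about 4 more patients through surgery before any review.

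The cost is a protocol amendment and one further reading by the surgeon already appointed, with no new patients, visits or staff. No superiority claim is made at either look, so the final test needs no adjustment. Some exposure remains: the last third of patients would still be reviewed only at the final analysis. The choice of about 60 is a practical midpoint of the remaining accrual and is not derived from the documents.
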